### Data management, privacy, and confidentiality

REDCap’s secure, web-based platform used widely internationally, providing interfaces for validated data capture, role-specific access, audit trails for tracking data manipulation and exports, automated export procedures to SAS, and encrypted transmissions [90, 91]. Paper study documents such as signed informed consent forms will be stored in our secure research office once they are scanned into REDCap study files. Regular data quality checks, such as automatic range checks, will be performed by the study team to identify data that appear inconsistent, incomplete, or inaccurate.

Patients will not be identifiable in the project results database. The identifying information required for the clinical team to deliver the intervention will be kept in a separate database. Access to the final dataset will be restricted to the core research team.

### Statistical analyses

The reporting of the results of this trial will follow the CONSORT extension for pilot trials [92]. We will use descriptive statistics for presentation of baseline variables and adequacy of follow-up. Feasibility analysis, including recruitment rate (at least 30% of those eligible is considered success), participant retention rate (≥ 90% to end of study is considered success), and study resource utilization required (less than US $1500 CAD per patient recruited), will be descriptive.

Analysis will use intention-to-treat methods with censoring only if the patient dies or drops out of the study with refusal of negotiated further assessments. Costs and quality-adjusted life-years (QALYs) associated with the two interventions will be determined from a payer and societal perspective. Healthcare resource utilization collected as part of the trial will be costed using public data sources. Using information from the EQ-5D-5L, quality-adjusted life-years (QALYs) will be determined under an area under the curve approach.

Research staff and statisticians will review outcome data and analysis blinded to group identification. Given the short follow-up, low risk of the trial, and pilot design, no interim analysis or imputation for missing data is planned. All statistical analyses will be performed using SAS V9.4 software (SAS Institute Inc., Cary, NC, USA).

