**A. Feasibility outcomes**					
A1. Primary feasibility outcomes	A1.1 Participant recruitment rates	≥ 30% of those eligible will be considered success	Percentage recruited and rate of recruitment (of those screened, of those eligible, and of those approached)	Counts (%) over time	Baseline
	A1.2 Participant retention rate	≥ 90% is considered success	Percentage of those recruited who complete at least end-study outcome	Counts (%) end study	End of study
	A1.3 Intervention adherence	≥ 90% is considered success	Percentage of those recruited who completed each phase of the study (baseline, virtual visits, end of study outcomes)	Counts (%) over time	End of study
	A1.4 Study resource utilization	< US $1500 per patient recruited and completing the study	Study costs per patient recruited to end follow-up	Cost of personnel, supplies, travel, etc. to run the study	End of study
A2. Secondary feasibility outcomes	A2.1 Clinical Pharmacology & Toxicology (CPT) Recommendation Acceptance — Primary Team	> 50% medication recommendations	% CPT recommendations per patient accepted (continued or implemented)	Counts (%) after consult	Hospital discharge
	A2.2 CPT recommendation acceptance — patients	> 50% medication recommendations	% CPT recommendations per patient that were initially followed by patient	Counts (%) after consult	Hospital discharge
	A2.3 CPT recommendation adherence — Patients	≥ 90% is considered success	% CPT recommendations per patient still being followed at end of study	Counts (%)	End of study
	A2.4 CPT consultation volume capacity	Number of eligible patients available to approach is > 3 per day	Volume of eligible patients available to approach per week	Counts	Baseline
	A2.5 Potential to intervene entirely virtually	> 90% patients can be managed through follow-up entirely by virtual care platform	Number (%) patients entering follow-up who do not require an unscheduled in-person visit Number of follow-up visits conducted using secure videoconference platform	Counts (%)	End of study
**B. Clinical outcomes**		**Hypothesis**			
B1. Primary clinical outcomes	B1.1 Drug therapy problems improved	Intervention group will have more improved drug therapy problems compared to control group (e.g., dose adjusted, discontinued, interacting drugs removed)	Percentage of baseline drug therapy problems identified by APEQ that have been improved by end of study	Mean difference in APEQ score changes	End of study

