#### Primary outcomes

There are two types of primary outcomes that will be evaluated:The *primary feasibility outcomes* will be recruitment and retention rate for eligible patients and the estimated resources required per patient to complete the main trial (program delivery costs). We aim for at least 30% recruitment of those eligible, 90% retention of those recruited, and no more than US $1500 per patient spent on running the pilot trial. This figure is based on the limits of peer-reviewed RCT funding for a full trial.The *primary clinical outcome* will be the number of drug therapy problems remediated including the number of high-risk medications improved (for example, dose adjustment, discontinued, seriously interacting drugs removed) at 3-month posthospital discharge end-study visit, as judged by adjudicators using APEQ.

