### Follow-up

Patients will be followed until 3-month posthospital discharge or until death or admission to long-term care home, whichever occurs first. Follow-up visits will be conducted by videoconference via Epic EMR or Ontario Telehealth Network, or by phone call, depending on the patient’s digital technology capability.

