### Sample size

Since this is a pilot RCT, we will aim for 30 patients per group or 60 in total as this number is likely to provide adequate evidence regarding feasibility for ramp-up to a definitive trial.

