### Data collection methods

Trained research staff will conduct interviews with the patients or caregivers, entering data electronically on study laptops directly into REDCap case report forms. The participants’ medical records will be reviewed to abstract data on baseline characteristics, medical history, and medication information. Strategies to promote participant retention and complete follow-up include reminding participants in advance of their end-of-study visit and communicating by email if email address is provided at baseline. Participants who drop out of the study will have their data to that point retained in the study, as approved by REB, to avoid bias. The reasons for study non-completion will be recorded. The SPIRIT figure outlining the schedule of enrolment, intervention, and assessment (as per evidence-based recommendations for the minimum content of a clinical trial protocol) can be found in Table 3 [89].

**Table 3 Tab3:** IMPROVE-IT HRM schedule of enrolment, intervention, and assessment

**Assessment**	**Enrolment**	**Study in-progress**				**Study end**
	**Baseline**	**Inpatient stay**	**Hospital discharge**	**1 week**	**1 month**	**3 months**
Eligibility screen	A					
IMPROVE-IT assessment of capacity to consent	B					
Informed consent	1/C					
EQ-5D-5L v10- Canada	I/C					I/C
Medication quality of life (MedQOL)	1/C					I/C
Clinical Frailty Scale	I/C					I/C
Complete medication list (prescription, OTC, other)	I/C		I/C			I/C
Medication knowledge assessment	I/C					I/C
Circle-of-care information	I		I	I	I	
Randomization and allocation	I/C					
Clinical Pharmacology Toxicology Consult		I		I	I	
Appropriateness of prescribing (APEQ) — #drug therapy problems improved, #high-risk medication problems improved, #PIMs improved	I/C					I/C
Adverse drug event assessment						I/C
Patient problems with medications						I/C
Patient/caregiver satisfaction questionnaire						I/C
Provider satisfaction questionnaire						I/C
Health Resource Utilization Questionnaire						I/C

Abbreviations: *A*-all potentially eligible patients, *B-*all eligible and interested patients, *I*-intervention, *C*-control, *I/C*-both groups

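### The follow-up and censoring rules conflict for long-term-care admission; the printed rules imply no QALY for patients who die, and count exits made by rule as retention failures

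*Protocol article*

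**What the plan says.** Four parts of the protocol article bear on this point.

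- **Follow-up section:** "Patients will be followed until 3-month posthospital discharge or until death or admission to long-term care home, whichever occurs first".
- **Statistical analyses section, censoring:** "Analysis will use intention-to-treat methods with censoring only if the patient dies or drops out of the study with refusal of negotiated further assessments". LTC admission is not on this list.
- **Statistical analyses section and Table 3, QALYs:** "quality-adjusted life-years (QALYs) will be determined under an area under the curve approach", and "no interim analysis or imputation for missing data is planned". The Table 3 row "EQ-5D-5L v10- Canada" has entries at baseline and 3 months and nowhere between.
- **Table 2, row A1.2, retention:** "Percentage of those recruited who complete at least end-study outcome", with success at 90% or more. The Primary outcomes section repeats the target as "90% retention of those recruited". Neither place exempts patients whose follow-up ended through death or LTC admission.

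The Participants section excludes patients being discharged to LTC, so a later LTC admission is governed only by the follow-up rule. Table 1 lists death among the clinical events recorded under health resource utilization.

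**The concern.** A patient admitted to LTC in week 5 is no longer followed under one section and may not be censored under another. Both rules cannot be applied to that patient.

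For a patient who dies, the sections agree with each other, but the result is unsatisfactory for QALYs. Death is an observed outcome with a known utility afterwards. Treating it as censoring, with no second EQ-5D-5L value and no imputation, leaves nothing from which to compute an area under the curve. The cost per QALY (Table 2, row B2.10, judged against US $50,000) would then describe only patients assessed at 3 months. Any difference in mortality between arms would disappear from it.

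For retention, a patient whose follow-up the plan itself ended is counted in the same way as one who walked away. The criterion then mixes mortality and placement with the trial's ability to keep participants, and it is one of the primary feasibility outcomes.

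**Working it through.** **1. The rules side by side**

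| Event before 3 months | Follow-up section | Statistical analyses section | Retention (A1.2) |
|---|---|---|---|
| Death | Ends follow-up | Censored | Not a completer |
| LTC admission | Ends follow-up | Not a permitted reason for censoring | Not a completer |
| Drop-out with refusal | Not listed | Censored | Not a completer |

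The direct contradiction is in the LTC row only.

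**2. Retention arithmetic**

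Inputs: N = 60 (Sample size section: "we will aim for 30 patients per group or 60 in total") and a threshold of 90%. The sample size is a pragmatic pilot figure with no power calculation behind it, so there is nothing to reproduce beyond 2 × 30 = 60.

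Completers needed: 0.90 × 60 = 54, so at most 6 losses from any cause. Seven losses give 53/60 = 88.3%, which fails.

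Let q be the probability of death or LTC admission by 3 months and w the drop-out probability among the rest. The article gives neither, so both are assumed over a range. The chance of failing is P(X ≥ 7) with X ~ Binomial(60, 1 − (1 − q)(1 − w)).

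| Assumed q | Fails, w = 0 | Fails, w = 5% |
|---|---|---|
| 3% | 0.002 | 0.19 |
| 5% | 0.03 | 0.37 |
| 8% | 0.20 | 0.64 |
| 10% | 0.39 | 0.79 |
| 15% | 0.82 | 0.96 |

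For comparison, if patients who left by rule are taken out of the denominator, a trial with 5% drop-out passes with probability about 0.94 at every q in the table, so it fails about 6% of the time.

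**3. QALY illustration**

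Assumptions, none from the article: constant utility u, death halfway through the 3 months (0.125 years), utility zero afterwards.

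- QALY of a survivor: 0.25u. At u = 0.6 this is 0.15.
- QALY of a patient who dies: 0.125u. At u = 0.6 this is 0.075.
- Loss per death: 0.125u. At u = 0.6 this is 0.075.

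With mortality of 5% in one arm and 15% in the other, the true difference is 0.10 × 0.125u. That is 0.00625 at u = 0.5, 0.0075 at u = 0.6 and 0.00875 at u = 0.7. At US $50,000 per QALY, 0.0075 is worth US $375 per patient. With equal survivor utilities, an analysis restricted to survivors gives a difference of exactly 0 in each case. With equal mortality (10% in both arms) the between-arm difference is also 0 when deaths are included, so the distortion depends on a mortality imbalance.

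**The case against.** **Death.** It would be wrong to say that the plan contradicts itself on death: both sections stop there. Nor does the article state that QALYs will be computed in survivors only. A reader might infer it as a stated decision, but it is a consequence of four printed rules taken together. One can also argue that death is not missing data, so the ban on imputation does not touch it, and that a fuller analysis plan may assign zero after death. That is possible, but such a plan would have to qualify the censoring sentence printed here, so the sentence still needs amending.

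**LTC.** A softer reading treats LTC admission as a planned end point of follow-up and the censoring sentence as covering only observation cut short. Ending follow-up there also fits the exclusion of settings where neither patient nor caregiver controls the medications. The conflict could therefore be resolved in either direction, but the word *only* in the censoring sentence means that one of the two must change.

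**Retention.** A denominator of everyone recruited is a transparent and conservative choice. The Data collection methods section records reasons for non-completion, and the feasibility analysis is descriptive, so a shortfall caused by deaths would be visible. This largely stands: the definition is defensible. What is missing is any statement of whether exits made by rule are meant to count against the trial.

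**Size.** A reader might infer that the retention criterion is likely to fail. The article gives no death or LTC rate. At 3% to 5% with no drop-out the criterion passes 97% to 99.8% of the time, and excluding patients discharged to LTC limits early placements. The QALY figure rests on an assumed mortality difference of 10 percentage points.

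**Conclusion.** The point holds in a limited form and should be fixed. The LTC conflict is a plain contradiction in the text. The absence of a QALY for patients who die is a sound inference from the printed rules, and it is inconsistent with the intention-to-treat claim made in the same sentence as the censoring rule. The retention result is arithmetic: 7 deaths or LTC admissions fail the criterion with perfect participant cooperation. How likely that is depends wholly on an unstated rate: negligible at 3%, about two in five at 10%, and four in five at 15%.

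It is not a fault that invalidates the trial. Cost-effectiveness is a secondary outcome of a 60-patient feasibility pilot, the QALY effect appears only if mortality differs between arms, and the all-recruited retention figure is worth having in its own right.

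**What to change.** 1. **LTC.** Make the Follow-up and Statistical analyses sections agree. The preferable route is to collect 3-month outcomes, events and costs after LTC admission by chart review and caregiver interview, because this keeps the patient in the intention-to-treat analysis. The alternative, adding LTC admission to the censoring list, removes the contradiction but loses what happens after placement.
2. **Death.** State that utility is zero from the date of death, that costs are counted up to death, and that patients who die are included in QALYs and costs. Limit the word *censoring* to patients whose later status is truly unknown.
3. **Retention.** Keep the all-recruited figure, add retention among patients alive at 3 months, and report deaths and LTC admissions by arm. State before the data are seen which of the two figures the 90% criterion uses.

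The cost is a few sentences of protocol wording and a small number of extra calls or record requests for patients admitted to LTC. Randomization, sample size and visit schedule are unchanged.

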### Data monitoring

Any serious adverse event will be reviewed by our Trial Steering Committee (TSC) within 48 h of detection, to discern any attribution to our procedures. If found to be due to our coordination procedures, the Trial Steering Committee will recommend whether modifications are indicated. The TSC will be composed of individuals with expertise in clinical trials, chaired by the lead statistician, and include the PI, the operational statistician, plus a methodologist independent of the study team. Similarly, since this is a short pilot pragmatic RCT where no harm is expected and adjustment of trial procedures may be necessary for feasibility, no formal external auditing of trial conduct is planned. There is no requirement for additional ancillary and posttrial care for those who might come to harm while in the trial, as usual medical care which covers this eventuality is already in place.

#### Impact of research

By creating a network of clinicians, patients, researchers, drug policy advisors, information technology advisors, quality improvement advisors, and hospital and national medication safety administration, we hope to strengthen and broaden the usual dissemination of research to practice We expect the pilot study to inform a future definitive trial by identifying solutions to overcome potential limitations including the following:The CPT team is a scarce resource which limits eventual generalizability. Based on pilot results, we will plan to study how physician assistants and clinical pharmacists can be trained to do this work.The short follow-up of 3 months is typical of transitional care initiatives but may be too short to show impact on clinical outcomes.The single-center design aids feasibility of the pilot but limits generalizability. A larger trial, if feasible, will aim to recruit other hospitals using the Epic EMR or members of the national deprescribing network.A definitive trial will highlight clinical outcomes as primary outcomes.

## Data Availability

An anonymized dataset will be shared in accordance with future requirements of our funders, the Canadian Institutes of Health Research.

## Abbreviations

ADE: Adverse drug event
APEQ: Appropriateness of Prescribing Evaluation Questionnaire
CPT: Clinical pharmacology and toxicology
EMR: Electronic medical records
EQ-5D-5L: European Quality-of-Life Five Dimension
HRM: High-risk medication
NCC-MERP: National Coordinating Council for Medication Error Reporting and Prevention
PIM: Potentially inappropriate medication
QOL: Quality of life
RCT: Randomized control trial
REDCap: Research Electronic Data Capture
SD: Standard deviation
STOPP: Screening Tool of Older People’s Prescriptions
WHO: World Health Organization
